### Statistical Approach

The primary endpoint this study is powered for is the estimated 24-hour urinary excretion of sodium from spot urine. Based on the data in patients with hypertension, we conservatively expect the 24-hour urinary excretion of sodium to decrease from 3400 (SD 1200) mg/24 hours to 2400 (SD 1200) mg/24 hours (35% reduction in sodium intake) in the mobile app group and a decrease from 3400 (SD 1200) mg/24 hours to 3300 (SD 1200) mg/24 hours in the usual care group [30]. The total sample size of 24 patients (12 in each group) and 32 patients (16 in each group) will provide 80% and 90% power, respectively, for a 35% reduction in sodium intake. In order to account for patients dropping out or incomplete follow-up, we are enrolling a total sample of 50 patients (25 in each group). We will use a two-sided *t* test to compare the change in each outcome over time in the mobile app group versus the usual care group. Other quantitative measures of sodium intake will be 24-hour urinary excretion of sodium and estimated 24-hour urinary excretion of sodium from chloride and creatinine dipsticks, which will be analyzed using a two-sided *t* test and repeated measures analysis of variance, respectively.

Although not powered to determine the impact, other measures of the effectiveness of this intervention will be summarized and evaluated. The percent change in confidence following a low-sodium diet will be analyzed using a two-sided *t* test. The change in blood pressure over time will be analyzed using repeated measures analysis of variance.

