### General Design

This is a single-center, prospective, open-label designed clinical trial. Recruitment is being performed at the University of Michigan Health System through our patient recruitment platform and recruitment letters to patients that meet our study criteria. Enrolled patients will be randomized to the mobile app or usual care in a 1:1 fashion using the University of Michigan Consulting for Statistics, Computing and Analytics Research randomization tool. Patients randomized to the mobile app will receive a 30-minute training session about the mobile app and be instructed to use the mobile app for 8 weeks. To address the research bias in this unblinded trial, all primary outcomes measured are objective. Some outcomes are not objective and represent a limitation of this research. This study was approved by the University of Michigan Institutional Review Board.

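### The 35% reduction for which power is claimed does not follow from the stated means, which give 29% in the app group and 900 mg between groups

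*Protocol article*

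**What the plan says.** All the figures are in the Statistical Approach section of the protocol article and concern the primary endpoint, 24-hour urinary sodium excretion estimated from spot urine.

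- App group: starting at 3400 mg (SD 1200), the expected follow-up value is given as "2400 (SD 1200) mg/24 hours (35% reduction in sodium intake) in the mobile app group".
- Usual care: the plan expects "a decrease from 3400 (SD 1200) mg/24 hours to 3300 (SD 1200) mg/24 hours in the usual care group".
- Power: "The total sample size of 24 patients (12 in each group) and 32 patients (16 in each group) will provide 80% and 90% power". The effect named for both of these claims is the same percentage again: "for a 35% reduction in sodium intake".
- Dropout allowance: "we are enrolling a total sample of 50 patients (25 in each group"), with no attrition rate given.
- Test: two-sided, described as a t "test to compare the change in each outcome over time in the mobile app group versus the usual care group".

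The section does not state the alpha, the SD of the change, or the correlation between baseline and follow-up.

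**The concern.** The percentage contradicts the means printed beside it, and it is then reused in the power sentence. That sentence names no difference in mg, so the wrong percentage is the only effect size attached directly to the 80% and 90% claims. A reader who takes it literally works with 1190 mg. A reader who takes the means works with 1000 mg within the app group, or 900 mg between groups. The largest of these is 1190/900 = 1.32 times the smallest, which matters for anyone checking whether 25 per group is enough. The direction also matters: 35% is larger than anything the stated means support, and the test works on the smallest of the three differences.

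**Working it through.** **Inputs (Statistical Approach).** Baseline 3400 mg in both groups; follow-up 2400 mg (app) and 3300 mg (usual care); SD 1200 mg at each time point; 12 or 16 per group for 80% or 90% power; 25 per group enrolled; two-sided t test on change. Allocation is 1:1 (General Design).

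**Assumed, because not stated.** Alpha 0.05. SD of change = 1200 × √(2(1 − ρ)), where ρ is the correlation between baseline and follow-up. This equals 1200 mg only when ρ = 0.5.

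**Step 1: the percentage.**
- App group: (3400 − 2400)/3400 = 1000/3400 = 29.4%.
- A 35% fall: 0.35 × 3400 = 1190 mg, ending at 3400 − 1190 = 2210 mg.
- Between groups: 1000 − 100 = 900 mg, and 900/3400 = 26.5% of baseline.

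Other routes to 35% fail. Rounding 29.4% does not reach it. Dividing by the follow-up value gives 1000/2400 = 41.7%. Reading it as intake rather than excretion changes nothing if the excreted fraction is constant, because the fraction cancels. The log ratio ln(3400/2400) = 0.348 is close, but it is not a percent reduction and the article mentions no log scale.

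**Step 2: can the stated 12 and 16 per group be reproduced?** Two-sample t test (noncentral t), SD of change 1200 mg:

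| Difference | n per group, 80% | n per group, 90% |
|---|---|---|
| 1190 mg (35%) | 17 | 23 |
| 1000 mg (app group alone) | 24 | 32 |
| 900 mg (between groups) | 29 | 39 |
| Stated in the plan | 12 | 16 |

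No row matches.

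**Step 3: what SD of change would reproduce them?** A t test with 12 per group and 80% power needs a standardised difference of about 1.20; 16 per group and 90% power needs about 1.18. Dividing each difference by these values:
- 900 mg: SD of change 752 to 760 mg, ρ about 0.80.
- 1000 mg: 836 to 844 mg, ρ about 0.75.
- 1190 mg: 994 to 1005 mg, ρ about 0.65.

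**Step 4: power for the 900 mg difference.**

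| ρ | SD of change (mg) | 12 per group | 16 per group | 25 per group |
|---|---|---|---|---|
| 0 | 1697 | 24% | 31% | 45% |
| 0.3 | 1420 | 32% | 41% | 59% |
| 0.5 | 1200 | 42% | 54% | 74% |
| 0.6 | 1073 | 50% | 63% | 83% |
| 0.7 | 930 | 62% | 76% | 92% |
| 0.8 | 759 | 79% | 90% | 98% |

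The column for 25 per group is before any dropout.

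**The case against.** The strongest defence is that this is a wrong label beside explicit means. The means for both groups are printed, so 1000 mg and 900 mg can be read off. Correcting the label changes neither the enrolment, the test nor the endpoint. At its first use the percentage describes the app group alone, and a within-group percentage is not wrong merely because it differs from the between-group one. All of this stands. The defence does not cover the second use, where the 35% is the only effect attached to the power claim and no group or mg figure accompanies it.

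Several stronger readings are tempting, and the article does not support them.

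- *The 35% figure inflated the sample-size calculation.* Taking the printed SD as the SD of change, 1190 mg needs 17 and 23 per group, not 12 and 16. A smaller SD of change, near 1000 mg, would fit 1190 mg, but other SDs fit 1000 mg or 900 mg equally well. The article does not show which effect was used.
- *The trial is underpowered.* The 74% at 25 per group rests on ρ = 0.5. At ρ = 0.6 it is already 83% before dropout. No correlation is given.
- *The totals of 24 and 32 are really per-group numbers.* They do equal the per-group sizes for 1000 mg at SD 1200, which is worth asking the sponsor about. A higher correlation explains the stated figures too, so the match is not proof.
- *A 29% fall would count as failure.* No success threshold of 35% is set; the analysis is a between-group t test.
- *The plan is wrong to call its expectation conservative.* That depends on the cited data in patients with hypertension, and the arithmetic here does not bear on it.

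**Conclusion.** The error is certain and needs no assumption: 35% should be 29.4% (1000 mg) in the app group, and the contrast under test is 900 mg (26.5% of baseline). The wrong percentage is more likely a label than the input to the sample size, although the article cannot settle this.

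Correcting the label alone is not enough, because the stated power would then be attached to 900 mg, where it holds only if ρ is about 0.80. At 16 per group the power for 900 mg runs from 31% (ρ = 0) to 90% (ρ = 0.8), with 54% at ρ = 0.5. These power figures assume two-sided alpha 0.05, equal group sizes and the printed SD of 1200 mg at both time points. The point is worth correcting, but it does not undermine the design.

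**What to change.** In both places in Statistical Approach, replace the 35% figure with a 29% (1000 mg) reduction in the app group and a 900 mg between-group difference. State the alpha and the SD of change (or the correlation) used, with the basis for it. Then restate the power of 12, 16 and 25 per group for 900 mg under those values. If a correlation near 0.80 was assumed, saying so would support the existing 80% and 90% to within rounding; if not, the figures need recalculating.

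The cost is a short recalculation and possibly a less favourable power statement. Enrolment of 50, the endpoint and the test stay as they are.

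### The stated 80% and 90% power at 12 and 16 patients per group does not follow from the printed figures; it needs an SD of change of about 755 mg that the article neither states nor supports

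*Protocol article*

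**What the plan says.** All the inputs stand in the Statistical Approach section of the protocol article.

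- Endpoint: "The primary endpoint this study is powered for is the estimated 24-hour urinary excretion of sodium from spot urine".
- App group: "decrease from 3400 (SD 1200) mg/24 hours to 2400 (SD 1200) mg/24 hours (35% reduction in sodium intake) in the mobile app group".
- Usual care: "a decrease from 3400 (SD 1200) mg/24 hours to 3300 (SD 1200) mg/24 hours in the usual care group".
- Test: "We will use a two-sided *t* test to compare the change in each outcome over time", app against usual care.
- Power claim: "The total sample size of 24 patients (12 in each group) and 32 patients (16 in each group) will provide 80% and 90% power", and this is said to be "for a 35% reduction in sodium intake".
- Enrolment: "In order to account for patients dropping out or incomplete follow-up, we are enrolling a total sample of 50 patients (25 in each group").

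The section gives no alpha, no SD of the change, no correlation between baseline and week 8, and no dropout rate.

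**The concern.** A t test on change needs two quantities: the difference between groups in mean change, and the SD of the change. The first follows from the printed means. The second is not printed; the article gives an SD of 1200 mg for the level at each visit. If 1200 is used, the claimed power is far out of reach at 12 or 16 per group. The effect is ambiguous as well, because the percentage attached to the power claim does not match the absolute figures.

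This is the power statement for the primary endpoint, and it presents 50 patients as a reserve above a need of 24 to 32. If that need is understated, some or all of the reserve does not exist, and a null result could be read as evidence against the app from a trial believed to be well powered.

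**Working it through.** **Inputs.** App change 3400 − 2400 = 1000 mg. Usual care change 3400 − 3300 = 100 mg. Difference in change Δ = 1000 − 100 = 900 mg. SD 1200 mg at each time point. Allocation 1:1. Two-sided alpha 0.05 is my assumption.

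**Formula.** With n per group and SD of change σ, power is the probability that a noncentral t variable with 2n − 2 degrees of freedom and noncentrality (Δ/σ)·√(n/2) falls beyond the two-sided 5% critical values.

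**Step 1: try to reproduce 80% and 90% with the printed SD.** Put σ = 1200, so Δ/σ = 900/1200 = 0.75.

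- n = 12: noncentrality 0.75 × √6 = 1.84, power 42.0%.
- n = 16: noncentrality 0.75 × √8 = 2.12, power 53.7%.
- n = 25: noncentrality 0.75 × √12.5 = 2.65, power 73.8%.
- Required n: 28.9, so 29 per group for 80%; 38.3, so 39 per group for 90%.

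The stated figures are not reproduced.

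**Step 2: more generous effects, still with σ = 1200.**

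| Difference | 12 per group | 16 per group |
|---|---|---|
| 900 mg (printed means) | 42.0% | 53.7% |
| 1000 mg (control change ignored) | 49.7% | 62.6% |
| 1190 mg (0.35 × 3400, no control change) | 64.1% | 77.5% |

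None reaches 80% and 90%.

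**Step 3: what SD of change would make the claim true at 900 mg?** 80% power at 12 per group needs Δ/σ = 1.197, so σ = 900/1.197 = 752 mg. 90% power at 16 per group needs Δ/σ = 1.185, so σ = 760 mg. With equal SDs of 1200 at both visits, σ = 1200·√(2(1 − rho)), hence rho = 1 − σ²/(2 × 1200²). This gives rho = 0.804 and 0.800. Forward at rho = 0.80, σ = 759 mg and power is 79.3% and 90.1%.

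**Step 4: a second possible origin.** For 1000 mg and σ = 1200 the required sizes are 23.6, so 24 per group, for 80% and 31.3, so 32 per group, for 90%. These are the two numbers that the article prints as totals.

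**Step 5: power at the enrolled size, 900 mg.** The 20-per-group column illustrates 20% dropout, which is an assumption.

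| rho | SD of change (mg) | 25 completers per group | 20 completers per group |
|---|---|---|---|
| 0.3 | 1420 | 59.3% | 49.8% |
| 0.5 | 1200 | 73.8% | 63.7% |
| 0.6 | 1073 | 82.8% | 73.4% |
| 0.7 | 930 | 91.8% | 84.7% |
| 0.8 | 759 | 98.4% | 95.5% |

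At 25 per group, 80% is reached at rho of about 0.57.

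**Step 6: the percentage.** 1000/3400 = 29.4%, not 35%. A 35% fall from 3400 is 1190 mg, to 2210 mg.

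**The case against.** The strongest reply is that 1200 mg is the SD of a level, not of a change. It equals the SD of change only if rho = 0.5, and the article does not say so. A single value, rho = 0.80, recovers both stated figures under the planned test with the correct 900 mg difference. On this view nothing was miscalculated; an input was left out of a condensed article whose fuller documents are not shown. The trial is also described as a pilot under Data Safety and Monitoring.

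Part of this stands. A reader might infer that true power at 12 and 16 per group is 42% and 54%, that 74% is the most the 50-patient trial can have, or that it has no dropout reserve. The article does not support these readings. Each treats 1200 as the SD of change; at rho 0.7, for example, 20 completers per group still have about 85% power.

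It does not rescue the claim. A correlation of 0.80 is stated nowhere and nothing in the article supports it. That it fits both figures is weak evidence, because any standardised effect giving 80% at 12 per group gives about 90% at 16. The point is also not mere omission: the article prints an SD and a power that do not go together, and leaves out the number that would connect them.

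A reader might likewise infer that per-group sizes were certainly printed as totals. The match in step 4 is exact, but the text gives the split into 12 and 16 per group explicitly, and this route also requires the 100 mg control change to have been ignored. It remains an inference that the sponsor can check.

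**Conclusion.** The point holds as a mismatch between the power claim and the inputs printed beside it. At 900 mg and an SD of 1200 mg, power is 42% and 54% rather than 80% and 90%, and neither a 1000 mg nor a 1190 mg difference closes the gap. The claim needs an SD of change near 755 mg.

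What power the trial really has cannot be settled from the article. It depends on rho, and 50 patients may be ample or too few: the reserve over 80% power exists only if rho exceeds about 0.57, before any dropout. The 35% label is a separate inconsistency in the same sentences. These results assume two-sided alpha 0.05 and, for the rho table, equal SDs of 1200 mg at both visits.

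**What to change.** Change the wording of the Statistical Approach section only:

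1. Withdraw the statement that 24 or 32 patients suffice, unless the SD of change behind it is stated and justified.
2. Check the original calculation for per-group sizes printed as totals.
3. State alpha, the 900 mg difference in change, and the assumed SD of change or rho with its source.
4. Reconcile the 35% label with the printed means.
5. Report power at 25 per group, and after a stated dropout allowance, over a range of rho such as the table above. Do not replace one unsupported value with another by fixing the SD of change at 1200 mg.

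Enrolment and conduct need not change. The cost is a short revision, and the published power figure may become less favourable.

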**Methods:**

In this single-center, prospective, open-label study, patients will be randomized to a mobile app or usual care for 8 weeks. We will randomize 50 patients (age>18 years) diagnosed with hypertension and on antihypertensive therapy for at least 3 months in a 1:1 manner stratified by gender. Study subjects will receive the mobile app, LowSalt4Life, or usual dietary advice for 8 weeks. LowSalt4Life provides a multifaceted intervention based on just-in-time contextual tailored messages at grocery stores and restaurants. The primary endpoint is the change in the estimated 24-hour urinary excretion of sodium from spot urine. Secondary outcomes include change in the sodium content of the food frequency questionnaire, confidence in following a low-sodium diet, urine chloride and creatinine dipsticks, and blood pressure.

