### Outcomes

The Automated Self-Administered 24-Hour Dietary Recall (ASA24), developed by the National Cancer Institute for dietary research, will be used to estimate the dietary sodium intake during the trial. The ASA24 is an electronic 24-hour recall website that allows patients to self-administer the survey in a user-friendly manner. The ASA24 allows researchers to send the survey at defined intervals and automatically performs a dietary analysis by converting the dietary recall data into nutrient information based on the Food and Nutrient Database for Dietary Studies. In order to provide a detailed interview, the website includes a meal-based quick list, meal gap review, review of forgotten foods, a final review, and a question about whether the day’s intake was usual or not. In this study, we will obtain the sodium content per day from the Food and Nutrient Database for Dietary Studies-based sodium content analysis completed by the ASA24 website. The ASA24 will be administered at week 0 and 8 of the study (see Figure 2 for details of outcomes).

The most widely used method for monitoring the sodium intake is urinary sodium excretion measured by a 24-hour urine collection. Patients will be instructed to collect all urine voids for 24 hours and return them for analysis for sodium excretion. In addition, the 24-hour urine excretion will be collected at baseline and after 8 weeks. This method is not convenient (eg, difficult to perform collections at work), and some participants may have incomplete urine collections. Owing to these challenges, we will also explore other methods to estimate sodium excretion that would be more practical for use in larger trials.

In addition to the gold standard, the first method to estimate the 24-hour urinary sodium excretion is spot morning urine excretion of sodium. The Kawasaki formula will be used to estimate the 24-hour sodium urinary excretion from a fasting morning urine sample [25]. This approach has been proven to provide a valid estimate of the sodium intake in several patient populations and in large-scale epidemiological studies [26]. Participants will be instructed to fast overnight, void in the morning, and provide us with a second morning urine sample on the day of the assessment. This measurement will be assessed at baseline and after 8 weeks of the study.

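### The t test on change is valid but less efficient than ANCOVA on baseline and gender, by an amount set by a correlation that the protocol does not state

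*Protocol article*

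**What the plan says.** The Statistical Approach section of the protocol article names the primary endpoint: "The primary endpoint this study is powered for is the estimated 24-hour urinary excretion of sodium from spot urine". The Outcomes section says of this spot-urine estimate: "This measurement will be assessed at baseline and after 8 weeks of the study". So every participant who completes follow-up has a baseline and a week-8 value.

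The planned comparison is a two-sided t "test to compare the change in each outcome over time in the mobile app group versus the usual care group". The same section names the t test again for measured 24-hour urinary sodium and for percent change in the confidence score. Sodium from the dietary recall (ASA24, weeks 0 and 8) is not named there and falls under the general statement. Dipstick sodium and blood pressure are assigned repeated measures ANOVA and lie outside this point.

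The Abstract says allocation is "in a 1:1 manner stratified by gender". General Design repeats the 1:1 ratio without mentioning strata. No stated analysis includes a baseline covariate or a gender term.

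For sample size, the protocol expects excretion "to decrease from 3400 (SD 1200) mg/24 hours to 2400 (SD 1200) mg/24 hours (35% reduction in sodium intake) in the mobile app group". For usual care it assumes a fall of 100 mg, to 3300 mg per 24 hours, with the same starting value and the same SD. It claims 80% power with 12 per arm and 90% with 16 per arm, and enrols 25 per arm to allow for dropout. It gives no SD of change, no correlation between the two measurements, no alpha and no dropout rate.

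**The concern.** A change score subtracts the whole baseline value. That is the best use of baseline only when baseline and follow-up are almost perfectly correlated. One spot-urine estimate at each of two visits eight weeks apart need not be. When the correlation is lower, subtraction over-corrects: it carries baseline noise into the outcome, and an arm that happens to start high tends to show a larger fall. ANCOVA estimates the baseline coefficient from the data and avoids both effects.

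The trial is small, so a loss of precision can matter, and the remedy uses data already being collected. The protocol also stratifies allocation by gender and then drops that factor from the analysis, so design and analysis do not match.

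**Working it through.** **Inputs.** SD 1200 mg at each time point, changes of −1000 mg (app) and −100 mg (usual care), and 25, 16 or 12 per arm are from Statistical Approach. The difference in change is 1000 − 100 = 900 mg. Two-sided alpha 0.05 is an assumption. Rho is not given, so a range is shown.

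**Formulas.**
- SD of change = 1200 × √(2(1 − rho))
- ANCOVA residual SD = 1200 × √(1 − rho²)
- Variance ratio, ANCOVA to change = (1 − rho²) / (2(1 − rho)) = (1 + rho)/2
- Power from the noncentral t distribution with noncentrality 900 / (SD × √(2/n)); 2n − 2 degrees of freedom for the t test, 2n − 3 for ANCOVA on baseline

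**The protocol's own figures first.** If 1200 mg is taken as the SD of change (rho 0.5), 12 per arm gives 42% power and 16 per arm gives 54%, not 80% and 90%. For a 900 mg difference the stated figures are recovered at rho of about 0.80: SD of change = 1200 × √0.4 = 759 mg, giving 79.3% at 12 per arm and 90.1% at 16. That rho is inferred. It depends on the difference used: the protocol calls the app-arm fall 35%, although 1000/3400 = 29.4%. If the calculation used 35% of 3400 = 1190 mg, the implied rho is about 0.65.

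**Power for 900 mg, t test on change → ANCOVA on baseline.**

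| rho | SD of change | ANCOVA SD | variance ratio | 25 per arm | 16 per arm | 12 per arm |
|---|---|---|---|---|---|---|
| 0.3 | 1420 | 1145 | 0.65 | 59.3% → 77.7% | 41.1% → 57.5% | 31.7% → 45.1% |
| 0.5 | 1200 | 1039 | 0.75 | 73.8% → 85.1% | 53.7% → 65.8% | 42.0% → 52.5% |
| 0.6 | 1073 | 960 | 0.80 | 82.8% → 90.1% | 63.1% → 72.7% | 50.2% → 59.1% |
| 0.7 | 930 | 857 | 0.85 | 91.8% → 95.3% | 75.5% → 81.9% | 62.1% → 68.9% |
| 0.8 | 759 | 720 | 0.90 | 98.4% → 99.1% | 90.1% → 92.7% | 79.3% → 83.1% |

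The ANCOVA figures charge the degree of freedom but not the average variance inflation from estimating the slope, a factor of 1 + 1/(2n − 4). At 25 per arm that is 1 + 1/46, about 2%, and it lowers the ANCOVA figures by less than one point. At 12 per arm it is 1 + 1/20, or 5%; at rho 0.8 the 83.1% becomes 81.3%.

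**Chance baseline imbalance.** The SE of the baseline difference at 25 per arm is 1200 × √(2/25) = 339 mg. A difference of one SE shifts the change-score estimate by (1 − rho) × 339 mg: about 170 mg at rho 0.5 (170/900 = 19% of the assumed effect) and 68 mg at rho 0.8 (8%).

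**Gender.** The term costs one further degree of freedom, 0.1 percentage point of power or less at 25 per arm. The document gives no sodium figures by gender, so no gain can be calculated.

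**The case against.** The strongest reply is that the planned test is sound and that the loss may be trivial. The first part stands. Under randomization the t test on change is unbiased, and leaving out a stratification factor keeps it valid and tends to make it conservative. The shift from baseline imbalance is conditional on the imbalance that happens to occur; it averages to zero over randomizations. A reader might infer that the planned estimator is biased, and the documents do not support that.

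A reader might also infer that baseline is ignored. It is not: a change score uses baseline, with a coefficient fixed at 1.

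On size, a reader might conclude that the trial has at most about 74% power and so must have the adjustment. But 74% is the value at rho 0.5, not a ceiling. At rho 0.8, which the protocol's own power figures imply for a 900 mg difference, the t test already has 98.4% power at 25 per arm and adjustment adds 0.7 points. If rho is in truth lower, the larger problem is the unsupported sample size calculation, which is a separate matter. What remains is that 0.8 is neither stated nor justified, and adjustment costs almost nothing if it is right.

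On gender, it is tempting to claim a definite gain in precision. Stable gender differences in sodium level largely cancel in a change score, and nothing in the document says that change differs by gender. Sex does enter the dipstick estimate, but through predicted creatinine, and that outcome is not assigned to the t test.

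Finally, this is a condensed article and a statistical analysis plan may add covariates. That would excuse silence. Here the article names a specific unadjusted test.

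**Conclusion.** The point holds as one of efficiency and of conditional imbalance, not of validity. Apart from the small cost of estimating one coefficient, ANCOVA is more precise than the planned test when rho is below 1.

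At 25 per arm the gain for the primary endpoint runs from 18 percentage points at rho 0.3, through 11 at 0.5 and 7 at 0.6, to 3.5 at 0.7 and under 1 at 0.8. At rho 0.5 the choice decides whether the trial passes 80% power with no dropout. At rho 0.8 it hardly matters unless dropout is heavy.

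These figures rest on an SD of 1200 mg at both time points, a 900 mg difference and an assumed two-sided alpha of 0.05. They apply to the primary endpoint; no such inputs are given for the other outcomes, and the confidence score is analysed as percent change, to which the variance ratio does not directly apply. The case for the gender term is consistency with the stratified allocation, not a demonstrated gain.

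**What to change.** For the primary endpoint, 24-hour urinary sodium, ASA24 sodium and the confidence score (SCFLDS), replace the t test on change with ANCOVA of the week-8 value on arm, baseline value and gender. Report the adjusted mean difference with its 95% CI. Keep the t test on change as a sensitivity analysis. State the SD of change, or the correlation, behind the 80% and 90% power figures.

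The cost is a change of wording and two degrees of freedom, with no new data. The Abstract reports 26 of 50 patients enrolled, so the change can still be pre-specified. Because the trial is open-label, it should be dated and fixed before any outcome is looked at by arm.

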**Objective:**

This study proposes that a mobile app intervention that promotes low-sodium alternatives at grocery stores and restaurants will reduce dietary intake of sodium and improve confidence following a low-sodium diet in hypertension.

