**Figure 2 figure2:**
[figure not shown]
Summary of outcomes in the trial. ASA24: Automated Self-administered 24-Hour Dietary Recall; FFQ: Food Frequency Questionnaire; SCFLDS: Self-Care Confidence in Following a Low-Sodium Diet Scale.

The second method for estimating the 24-hour urinary sodium excretion is with a spot urine sample using chloride and creatinine dipsticks. The dipstick method has been validated in patients with hypertension and correlates well with the 24-hour urinary sodium excretion (*r*=.86) [27]. The chloride dipstick is used as a surrogate for sodium excretion. The Quantab chloride dipstick (Hach, Loveland, CO, USA) is placed in a container filled less than halfway with urine. The chloride concentration is determined by observation of the change in color from brown to pale on the dipstick, which is the formation of silver chloride. The creatinine dipstick is similar to the chloride dipstick. The MultistixPro-10LS (Bayer, Elkhart, IN, USA) is a dipstick that includes a color pad for creatinine after it is placed in a container filled with urine. The color pad turns from yellow to green to indicate the creatinine concentration. The predicted 24-hour urinary sodium excretion is calculated on the basis of the 24-hour creatinine concentration calculated using sex, weight, race, and age. This model has been validated and correlates highly (*r*=.93) with 24-hour measurements of creatinine [28]. This measurement will be performed at baseline and after weeks 2, 4, 6, and 8.

The SCFLDS will be used to measure patients’ confidence in following a low-sodium diet. It assesses patients’ confidence in the ability to select and prepare low-sodium foods [29]. The tool consists of 7 items with 4 response options per item. The items ask patients to rate their level of confidence reading food labels, choosing low-sodium food during shopping, choosing low-sodium foods at restaurants, cooking low-sodium foods, choosing low-sodium foods at relatives or friends homes, estimating how much sodium they eat each day, and substituting low-sodium foods for high-sodium foods. The 4 response options are assigned a score of 1-4 (1=not confident; 2=somewhat confident; 3=very confident; 4=extremely confident) and then added for each question. Possible scores range from 7 to 28, and the higher score indicates greater confidence. The SCFLDS will be administered at baseline and after week 8 of the study.

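### Confidence is tested as unadjusted percent change on a 7-28 sum score with no true zero: a valid test, but equal gains count unequally and precision is lost that baseline adjustment on the points scale would recover

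*Protocol article*

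**What the plan says.** Outcomes (the text after Figure 2) defines the SCFLDS as seven items, each scored 1 to 4 and summed: "Possible scores range from 7 to 28, and the higher score indicates greater confidence". It is measured twice: "The SCFLDS will be administered at baseline and after week 8 of the study".

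Statistical Approach gives a general rule, a two-sided *t* "test to compare the change in each outcome over time in the mobile app group versus the usual care group". It then gives confidence its own sentence: "The percent change in confidence following a low-sodium diet will be analyzed using a two-sided" *t* test. No baseline covariate is named.

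Two statements set the weight of this outcome. The abstract's Objective says the app "will reduce dietary intake of sodium and improve confidence following a low-sodium diet in hypertension", and Aim and Hypothesis repeats confidence as part of the hypothesis. On the other side, the abstract's Methods list it as secondary, and the sentence just before the percent-change rule reads: "Although not powered to determine the impact, other measures of the effectiveness of this intervention will be summarized and evaluated".

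**The concern.** A ratio to baseline has meaning when zero means none of the quantity. Here the lowest possible total is 7, reached by answering at the bottom of every item. Dividing by that total gives each patient's gain a weight of 1/baseline, and the weight depends on an arbitrary origin.

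There are two consequences. First, the mean percent change is not a mean gain in confidence: patients who start low count for more, for no stated reason, and the result is hard to translate back into points. Second, dividing by a noisy baseline magnifies the variation among low starters, and the unadjusted *t* test does nothing to remove baseline variation. In a trial of 50 patients, precision is given away on an outcome named in the objective.

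**Working it through.** **Is there a stated figure to reproduce?** No. The article gives no mean, SD, correlation, effect size or power for the SCFLDS. The weighting below follows from the documented range alone. The power figures rest on assumed inputs.

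**Step 1. Unequal weighting.** Percent change = 100 × gain / baseline. For a gain of 4 points:

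| Baseline | Percent change |
|---|---|
| 7 | 400/7 = 57% |
| 14 | 400/14 = 29% |
| 24 | 400/24 = 17% |

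The same gain counts 24/7 = 3.4 times as much from 7 as from 24.

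**Step 2. Dependence on coding.** Score the same seven answers 0 to 3 instead of 1 to 4, so that every total falls by 7. A move from 14 to 18 becomes 7 to 11. The percent change goes from 4/14 = 29% to 4/7 = 57% although no answer has changed. The difference in points is 4 under either coding.

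**Step 3. Efficiency.** From the protocol: 25 per arm, scores bounded at 7 and 28, baseline and week 8 only. Assumed: two-sided alpha 0.05, baseline mean 14, SD 4.5, true gain over control 3 points, control drift +1 point, and correlation between baseline and week 8 of 0.4 to 0.6. Scores were simulated, rounded and clipped to 7-28, and three analyses were compared.

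| Correlation | *t* test, percent change | *t* test, raw change | ANCOVA on score |
|---|---|---|---|
| 0.4 | 45% | 57% | 70% |
| 0.5 | 52% | 64% | 74% |
| 0.6 | 62% | 74% | 81% |

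Repeat simulations agreed to within about 2 percentage points.

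**Step 4. Splitting the loss.** At correlation 0.5 the total loss is 74 − 52 = 22 points. Moving from percent to raw change, both unadjusted, recovers 64 − 52 = 12. Baseline adjustment recovers the other 74 − 64 = 10. At correlation 0.4 the split is 12 and 13; at 0.6 it is 12 and 7. The split depends on the order of the steps. If baseline is adjusted first, ANCOVA on percent change reaches about 69%, against about 75% for ANCOVA on the score in the same run, so the scale then costs about 6 points.

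**Step 5. Wider assumptions.** The baseline mean was varied from 12 to 21, the SD from 3 to 5 and the correlation from 0.3 to 0.8, with the gain set so that ANCOVA had 74-79% power. Percent change then had 40-68% power, a loss of about 9 to 35 points. Letting the gain be proportional to baseline, the case most favourable in principle to a percent scale, still left a loss of about 7 to 30 points (means 12 to 18, SD 3 to 4, correlation up to 0.9).

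**Step 6. Validity.** With no treatment effect, all the analyses rejected about 5% of the time.

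**The case against.** The strongest reply is that little hangs on this. Confidence is secondary, the protocol says these measures are not powered, Data Safety and Monitoring calls the trial a pilot, and no success criterion depends on this *p* value. That stands and limits the weight of the point. It does not defend the choice: a test is still planned, and the better analysis uses data already being collected.

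Several stronger readings are tempting, and the documents do not support them.

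- *The whole power loss is due to the percent scale.* It is not. Comparing percent change with ANCOVA alters the scale and the adjustment together. Missing baseline adjustment is common to the other *t* tests in the section.
- *The test is invalid or biased because percent change is skewed.* Randomisation protects it, and simulated type I error is about 5%. A chance imbalance in low baselines is a matter of precision, and it affects unadjusted raw change as well.
- *The ceiling condemns percent change.* A patient at 24 can gain at most 4 points on any metric, and ANCOVA on the score does not remove that limit.
- *The section contradicts itself.* A reader might set the percent-change sentence against the general rule on change in each outcome. The section also gives specific rules for the dipsticks and blood pressure. A specific sentence refining a general one is ordinary drafting, and the confidence sentence is clear.

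**Conclusion.** The point holds as one of scale and efficiency. The unequal weighting and the dependence on item coding follow directly from the documented 7-28 range and need no assumption. The direction of the power loss is robust: percent change was below ANCOVA on the score in every scenario with a true effect. Its size is not known, because the article gives no SCFLDS parameters. It is about 19 to 25 points in the assumed central case and about 7 to 35 points across the wider ranges. In the central case roughly half belongs to the percent scale when neither analysis is adjusted, and less (about 6 points) once baseline is adjusted. The planned test is not wrong in the sense of producing false positives, and the outcome is secondary and declared unpowered, so this is an improvement worth making rather than a threat to the trial's main conclusion.

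**What to change.** Replace the percent-change sentence with an ANCOVA of the week-8 SCFLDS total on treatment, baseline SCFLDS total and gender (the stratification factor given in the abstract's Methods). Report the adjusted between-group difference in points with its 95% confidence interval. Keep percent change, if wanted, as a descriptive summary only.

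The cost is one sentence in the analysis plan. Baseline and week-8 scores are already collected, so no visit, form or sample size changes. Because the trial is open-label and already enrolling, make and date the change before any outcome is compared by arm.
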